**Primary outcome [3]**

Breast cancer worry

The following item will be used to measure breast cancer worry.

How worried would you be about developing breast cancer after receiving this letter? 4-point scale (1 = 'strongly agree' to 4 = 'strongly disagree')

Reference: Sutton S, Bickler G, Sancho-Aldridge J, Saidi G. Prospective study of predictors of attendance for breast screening in inner London. Journal of Epidemiology & Community Health. 1994;48(1):65-73.

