### Outcome measures:

Variable name in SPSS in *light blue*

Variable for comparison: condition (*condition*)

Primary outcomes:

- intentions to seek supplemental screening (*Intent\_Screen\_SuppScreen*)
- psychological outcomes
  - feeling anxious (*Anxiety*)
  - feeling informed (*Informed*)
  - feeling confused (*Confusion*)
- breast cancer worry (*CancWorryAfter*)

Secondary outcomes:

- intention to speak to a GP (*Intent\_TalkGP*)
- breast density knowledge
  - Knowledge about percentage (*BDKnowl\_Percentage*)
  - Knowledge about cancer risk (*BDKnowl\_CancRisk*)
  - Knowledge about masking (*BDKnowl\_Masking*)
  - Knowledge about age (*BDKnowl\_Age*)
- Cancer risk perception (*Percep\_CancRisk*)

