### Specific research questions:

1. Do outcomes relating to intention to seek supplemental screening, feelings of being anxious, informed or confused, breast cancer worry, breast density knowledge, cancer risk perception and intention to speak to a GP differ between women who received screening mammography results with or without breast density messaging?
2. Do outcomes relating to intention to seek supplemental screening, feelings of being anxious, informed or confused, breast cancer worry, breast density knowledge, cancer risk perception and intention to speak to a GP differ between women who received existing breast density notification messaging and health literacy sensitive breast density messaging?
3. Do women's breast cancer worry differ before and after the breast density notification?  
Does the difference vary depending on which messaging they receive?
  - Intervention (*condition=2* or *condition=3*)
  - Cancer worry before intervention (*CancWorryBefore*)
  - Cancer worry after intervention (*CancWorryAfter*)

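### The before/after part of SAP question 3 leaves out the control arm, so on its own it cannot isolate the effect of the density letter on worry

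*Combined protocol and SAP*

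**What the plan says.** The SAP, under Specific research questions, question 3, has two parts. The first asks: "Do women's breast cancer worry differ before and after the breast density notification". The second asks: "Does the difference vary depending on which messaging they receive". The groups listed beneath are "Intervention (*condition=2* or *condition=3", and the variables are a baseline item, "Cancer worry before intervention (*CancWorryBefore", and its post-intervention counterpart. Condition 1, by inference the control arm, is not listed.

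Other parts of the plan bear on this:

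- Question 1 covers the same worry outcome and asks whether it will "differ between women who received screening mammography results with or without breast density messaging". That comparison includes the randomised control.
- The SAP's primary outcome list names "breast cancer worry (*CancWorryAfter", the post-letter value and not the change. The baseline variable appears only under question 3.
- The registration, under Statistical methods / analysis, plans regression contrasts of each intervention arm against control.
- The registration gives the after item, under Primary outcome [3], as "How worried would you be about developing breast cancer after receiving this letter".
- The registration's description of the interventions says that all three arms read the same clear-result letter, and that arms 2 and 3 also receive a density letter.

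**The concern.** A before/after change in arms 2 and 3 reflects everything between the two answers. That includes the clear-result letter, the density letter and being asked about worry a second time. It also includes the imagined screening visit, if the before item preceded it. Only the density letter is the notification that question 3 names. The control arm receives everything except that letter, so it is the group that can remove the rest.

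Without it, the first part of question 3 can err in either direction. It can show a change when the density letter does nothing. It can also show no change if the clear result lowers worry by as much as the density letter raises it. The question is not marked as descriptive or exploratory. The SAP also does not say which result takes precedence if questions 1 and 3 point different ways.

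**Working it through.** **Which contrasts have a randomised comparator**

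| Question | Contrast on worry | Randomised comparator? |
|---|---|---|
| 1 | Post-letter worry, with vs without density messaging | Yes, control |
| 2 | Post-letter worry, existing letter vs health literacy letter | Yes, the other letter |
| 3, first part | After vs before, within women in arms 2 and 3 | No |
| 3, second part | Change in arm 2 vs change in arm 3 | Yes, the other letter |

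Only one row lacks a comparator. Non-specific shifts common to the arms cancel in the other three.

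**The plan's own figure**

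The registration states n = 1398 for 80% power (read as such) at an adjusted alpha of 0.025. It gives no effect size, SD, event rates, sidedness or allocation ratio, so the figure cannot be reproduced from stated inputs. It can be back-solved. Assuming 1:1:1 allocation, 1398 / 3 = 466 per arm. At two-sided 0.025 the detectable standardised difference is

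(2.241 + 0.842) × sqrt(2/466) = 3.083 × 0.0655 = 0.202 SD.

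No figure is stated for question 3.

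**Illustration: how easily a non-specific shift would be significant**

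Assumptions, none of them in the documents: equal allocation, so 2 × 466 = 932 women in arms 2 and 3; a pooled paired test; two-sided 0.05; a normal approximation for a 4-point item; equal SD before and after; before/after correlation r; and a shift that has nothing to do with the density letter.

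SE of mean change, in SD units = sqrt(2(1 − r)/932)

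- r = 0.3: sqrt(1.4/932) = 0.0388
- r = 0.5: sqrt(1.0/932) = 0.0328
- r = 0.7: sqrt(0.6/932) = 0.0254

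Probability of significance = Phi(shift/SE − 1.96); the opposite tail is negligible.

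| Shift (SD) | r = 0.3 | r = 0.5 | r = 0.7 |
|---|---|---|---|
| 0.05 | 0.25 | 0.33 | 0.50 |
| 0.10 | 0.73 | 0.86 | 0.98 |
| 0.20 | >0.99 | >0.99 | >0.99 |

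For example, at r = 0.5 and a shift of 0.10: 0.10/0.0328 − 1.96 = 1.09, and Phi(1.09) = 0.86. Under the same conditions a comparison with control stays at its nominal level, whether it uses change or post-letter worry alone.

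**What adding control and baseline would give**

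Two-sided 0.025, 80% power, 466 per arm, each intervention arm against control:

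- Post-letter worry only: 0.202 SD, as above.
- Change score, multiplier sqrt(2(1 − r)): 0.202 × 1.000 = 0.20 SD at r = 0.5; 0.202 × 0.775 = 0.16 SD at r = 0.7.
- Adjusted for baseline worry, multiplier sqrt(1 − r²): 0.202 × 0.866 = 0.17 SD at r = 0.5; 0.202 × 0.714 = 0.14 SD at r = 0.7.

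The baseline-adjusted model is the most precise of the three at both correlations.

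**The case against.** The strongest reply is that the effect of notification on worry is already tested properly. Question 1 compares post-letter worry with and without messaging. Randomisation makes that valid without a baseline, and the masking described above cannot arise there because both sides read the same clear-result letter. This stands. A reader might infer from question 3 that the worry outcome has no comparator, or that the primary worry result is compromised. The documents do not support either inference.

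A reader might also infer that the sponsor means to credit any before/after change to the density letter. No section says how a change will be interpreted. Control women receive no density notification, so limiting a within-person question to arms 2 and 3 follows from its wording, and it can be read as descriptive. That also stands, but the SAP does not say so, and the wording of the question points to the notification.

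The second part of question 3 is a randomised contrast between letters, so question 3 is not uncontrolled throughout.

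Finally, the documents do not give the wording or exact position of the before item, or say whether control women answered it. A change of wording is therefore only a possible source of shift. The probabilities above show that about 900 paired answers will detect a small shift. They do not show that one exists. None of this repairs the first part of question 3, which has no comparator as written.

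**Conclusion.** The point holds for the first part of SAP question 3 only. That part cannot, by itself, separate the density notification from the scenario, the clear result or repeat asking. The primary worry contrast under question 1 and the between-letter part of question 3 are sound. Change in worry is not a listed primary or secondary outcome in the registration or the SAP.

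The restriction to conditions 2 and 3 is plain in the text. The size is illustrative: 73%, 86% and 98% for a 0.1 SD non-specific shift rest on the assumed shift, correlations, equal allocation, pooled paired test and two-sided 0.05. The point is worth correcting because the change is cheap and improves precision, but it ranks below a defect that must be fixed before the trial's main conclusions can stand.

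**What to change.** First establish whether CancWorryBefore was asked of all women.

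- **If it was:** include condition 1 in question 3. Fit one model of CancWorryAfter on the three arms, with CancWorryBefore as covariate. Report arm 2 vs control, arm 3 vs control and arm 3 vs arm 2. Present within-arm before/after change as descriptive only. Say how this model relates to the worry analyses under questions 1 and 2, so that each contrast has one designated answer.
- **If it was not asked in control:** label the first part of question 3 descriptive and state that causal statements about notification and worry rest on question 1. The comparison of change between the two letters can stay.

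The cost is a revision of the SAP wording and, in the first case, one model. No new data are needed in either case.
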